### 4.12. Statistical Analysis Plan

Consistent with the feasibility objectives of this trial, the primary analysis will focus on descriptive statistics, with feasibility outcomes compared against the predefined thresholds in Table 3 to guide progression to a definitive trial.

Secondary cognitive, functional, and psychological outcomes will be analysed using linear mixed-effects models (LMMs) to account for repeated measures and group differences. Fixed effects will include group (CT + iTBS, CT + sham-iTBS), time (baseline, post-iTBS, mid-intervention, post-intervention, follow-up), and their interaction. Participant ID will be modelled as a random effect. Model assumptions (e.g., normality of residuals, homogeneity of variance) will be tested and corrected as needed. Effect sizes will be estimated using Cohen’s d or f or partial η^2^ with 95% confidence intervals to inform sample size calculations for a future adequately powered trial. Analyses will be conducted using SPSS v25.0 (IBM Corp., IBM Corp., Armonk, NY, USA), Stata (StataCorp, College Station, TX, USA), or R (R Foundation for Statistical Computing, Vienna, Austria). *p*-values will be reported as nominal exploratory statistics and will not be interpreted as confirmatory evidence of efficacy. Covariates (age, sex, education) may be included in sensitivity analyses. Neurophysiological–cognitive correlations will be reported descriptively. Analyses will follow an intention-to-treat principle, with missing data handled using multiple imputation where appropriate.

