### 4.4. Outcome Measures

Outcomes will be assessed at 5 timepoints: baseline (Week 0), post-iTBS (Day 5, Week 1), mid-intervention (Week 5), post-intervention (Week 10), and follow-up (Week 18). As this is a feasibility pilot trial, the primary outcomes are feasibility, acceptability, adherence, and safety. The predefined progression (“stop/go”) criteria in Table 1, spanning recruitment, eligibility, adherence, tolerability, acceptability, and retention, will determine whether to proceed to a full-powered definitive trial, while safety is monitored throughout. Each primary domain is operationalised below.

**Feasibility (recruitment and retention).** Recruitment feasibility will be reported descriptively, including the number of participants registering interest, the proportion screened, eligibility yield, and the time taken to reach the target sample; these indicators establish whether recruitment is viable within the study’s eligibility constraints ahead of a definitive trial. Retention will be expressed as the proportion of randomised participants completing the post-iTBS (Week 1), post-intervention (Week 10), and follow-up (Week 18) assessments, and it will be evaluated against the attrition thresholds in Table 1.

**Adherence.** Adherence will be quantified as the proportion of scheduled iTBS and CT sessions completed, against the predefined thresholds in Table 1. iTBS attendance will be verified against site logs, while home-based CT completion will be captured automatically through the online training platform on a per-session basis. Missed sessions and the reasons for non-completion will be documented, and patterns of adherence across the intervention period, including session completion over time, drop-off, and whether adherence differs between the initial in-person sessions and the subsequent home-based period, will be summarised descriptively.

**Acceptability.** Acceptability will be evaluated using a post-intervention satisfaction scale and semi-structured exit interviews examining perceived burden, comfort, and willingness to participate again, and will be judged against the acceptability threshold in Table 1.

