**Safety and tolerability.** Safety will be monitored at every iTBS session and throughout the follow-up period; participants will be asked to report adverse sensations (e.g., headache, scalp discomfort, tingling, and fatigue), and all adverse events (AEs) will be reviewed for severity and relatedness and managed in accordance with the safety procedures described in Section 4.10. Tolerability will be operationalised as the proportion of withdrawals that are not attributable to intervention-related AEs, and will be evaluated against the threshold in Table 1.

Secondary outcomes include cognitive measures of verbal memory (CVLT-II), and episodic memory (RBANS Story Recall), executive function and processing speed (D-KEFS TMT; WAIS-IV Coding, Similarities; Digit Span), functional independence (HBA-FAQ), psychological well-being (PHQ-9, GAD-7, PSQI), and health-related quality of life (EQ-5D-5L). All measures were selected based on clinical relevance and psychometric properties (Supplementary Table S1). These outcomes are exploratory and are included not to establish efficacy but to estimate the magnitude and variability of potential change and to inform outcome selection and sample-size estimation for a future definitive trial. Exploratory signals of change will be characterised using effect size estimates (Cohen’s d) with means, standard deviations, and 95% confidence intervals.

Tertiary outcomes are mechanistic and include neurophysiological measures of cortical excitability and inhibition using paired-pulse TMS paradigms, including short- and long-interval intracortical inhibition (SICI, LICI), resting-state EEG and event-related potentials (ERPs) recorded during cognitive tasks. Given the feasibility design, these neurophysiological measures are exploratory and hypothesis-generating. They are intended to determine which markers can be feasibly acquired and are worth retaining as mechanistic outcomes in a definitive trial.

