### 4.6. Participant Timeline

Following eligibility screening and informed consent, baseline assessments will be completed before randomisation. Baseline cognitive assessments will be completed during Week 0, and baseline EEG and TMS will be conducted on Day 1. Participants will then be randomised 1:1 into one of two groups, with the first active or sham iTBS session delivered immediately following randomisation. The intervention begins in Week 1, with active or sham iTBS delivered over 5 consecutive weekdays (Days 1–5). EEG and TMS will be repeated on Day 5 to evaluate short-term effects.

Participants will then complete 9 weeks of home-based CT (Weeks 2–10), with a mid-intervention EEG/TMS at Week 5. At the end of Week 10, post-intervention assessments will include cognitive testing, EEG, and TMS. At Week 18, all assessments will be repeated to evaluate durability of effects. The overall participant flow is summarised in Figure 2 and the Schedule of Activities in Table 4. A complete visual overview of the study design and schedule is provided in Figure S1 (Supplementary Materials).

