### 4.7. Sample Size

As this is a feasibility pilot trial, the sample size was not determined by formal power calculations for hypothesis testing. Sample size determination in pilot studies is typically based on practical considerations, study logistics, and precedent rather than statistical power, with 12 participants per group recommended as a reasonable minimum [48]. Feasibility and pilot trials using iTBS and rTMS in MCI have employed sample sizes ranging from 18 to 38 participants [49]. A sample of 44 participants (22 per group) is consistent with and exceeds these precedents, and is sufficient to characterise feasibility outcomes, estimate variability in cognitive measures, generate preliminary effect size estimates, and is expected to provide preliminary neurophysiological data to inform the design of a future definitive trial. An anticipated dropout rate of ~20% has been accounted for [50], and effect size estimates will build on a pooled effect size of g = 0.36 for CT in MCI [11] to inform a future definitive trial.

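### The screening HBA-FAQ and PHQ-9 scores have no role in the mixed model; using them could modestly sharpen two exploratory arm contrasts, though the gain is not assured

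*Protocol article*

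**What the plan says.** Section 4.4 of the protocol article names both scales as secondary outcomes: "functional independence (HBA-FAQ), psychological well-being (PHQ-9, GAD-7, PSQI", with EQ-5D-5L for quality of life. HBA-FAQ is the only measure listed there for functional independence.

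Table 4 marks HBA-FAQ at screening, Week 0, Week 10 and Week 18, and PHQ-9 at the same visits plus Week 5. Section 4.6 states that "baseline assessments will be completed before randomisation", so each scale has two readings before allocation.

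Section 4.4 labels Week 0 as baseline and does not count screening among the five outcome timepoints. Section 4.12 carries those timepoints into the model as "time (baseline, post-iTBS, mid-intervention, post-intervention, follow-up), and their interaction". It adds that "Participant ID will be modelled as a random effect" and that "Covariates (age, sex, education) may be included in sensitivity analyses". On this text the screening score is neither a time level, nor a covariate, nor part of the baseline value.

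**The concern.** A score taken before randomisation cannot be affected by treatment. Where it carries information on later scores beyond what Week 0 carries, using it narrows the interval for the arm comparison at no cost in visits or testing.

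The stake is small but fits the trial's stated purpose. Sections 4.4 and 4.12 want effect sizes with 95% confidence intervals for function and mood to help plan a definitive trial, and about 35 of the 44 participants would remain after the expected 20% dropout (44 × 0.8 = 35.2).

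**Working it through.** **Inputs.** 44 participants, 22 per arm (Section 4.7). Two pre-randomisation readings per scale (Table 4). A random participant effect (Section 4.12), which implies the same correlation ρ between any two visits. ρ is not in the documents and is assumed. Outcome SD is set to 1. The plan states no precision figure for either scale, and for the trial as a whole "the sample size was not determined by formal power calculations for hypothesis testing", so there is nothing to reproduce first.

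**Equal correlation.**
- Change from one reading: 2(1−ρ). Change from the mean of two: 1 + (1+ρ)/2 − 2ρ = 1.5(1−ρ). The ratio is 0.75, a 25% cut at any ρ, equivalent to 44/0.75 ≈ 59 participants. The standard error √(2v/22) goes from 0.302 to 0.261 SD at ρ = 0.5, and from 0.234 to 0.202 at ρ = 0.7.
- Adjusted for one reading: 1−ρ². Adjusted for two: 1 − 2ρ²/(1+ρ).

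| ρ | one | two | cut |
|---|---|---|---|
| 0.5 | 0.750 | 0.667 | 11% |
| 0.6 | 0.640 | 0.550 | 14% |
| 0.7 | 0.510 | 0.424 | 17% |
| 0.8 | 0.360 | 0.289 | 20% |

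These two sets of cuts do not add up. Adjusting for Week 0 alone already lowers the variance of the contrast as written by 25%, 15% and 10% at ρ = 0.5, 0.7 and 0.8. Only the table's last column belongs to the screening score.

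**Unequal correlation.** Screening lies 14 and 22 weeks before the Week 10 and Week 18 outcomes; Week 0 lies 10 and 18 weeks before. Write b for the Week 0–outcome correlation, s for screening–outcome and r for screening–Week 0. Then:
- change from the mean of two: 1 + (1+r)/2 − (b+s), against 2(1−b);
- adjusted for both, weights set by the data: 1 − (b² + s² − 2bsr)/(1−r²), against 1−b².

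| b, s, r | change | cut | adjusted | cut |
|---|---|---|---|---|
| 0.50, 0.48, 0.55 | 1.00 → 0.795 | 20.5% | 0.750 → 0.690 | 8.0% |
| 0.60, 0.55, 0.65 | 0.80 → 0.675 | 15.6% | 0.640 → 0.596 | 6.9% |
| 0.60, 0.50, 0.70 | 0.80 → 0.750 | 6.3% | 0.640 → 0.627 | 2.0% |
| 0.70, 0.50, 0.60 | 0.60 → 0.600 | 0% | 0.510 → 0.500 | 2.0% |

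The first three rows are illustrations within the ranges for decaying correlation (about 6 to 21% and 0 to 10%). The last is the unfavourable case. There, adjusting for the simple mean gives 1 − 0.60²/0.80 = 0.55 against 0.51 for Week 0 alone, about 8% worse.

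**Cost of the extra covariate.** One degree of freedom with 36 completers (18 per arm) costs about 1/(36−5) ≈ 3% of variance. The 11 to 20% cuts become about 8 to 17% (0.889 × 1.032 = 0.918; 0.802 × 1.032 = 0.828). A 2% cut becomes a loss of about 1%.

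**Selection at screening.** Simulation removing the worst 20% or 40% of screening values lowers the adjusted cut from 11% to 8% or 6% at ρ = 0.5, and from 20% to 16% or 14% at ρ = 0.8. Selection precedes randomisation and acts on both arms alike, so the arm comparison stays unbiased.

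**What does not help.** Adding screening as a sixth level of an unconstrained group-by-time model, with Week 0 still the reference, changes the variance by 0%.

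**The case against.** The time list in Section 4.12 is generic. It serves all secondary outcomes and includes the post-iTBS visit, where Table 4 schedules only TMS and EEG. Deriving a baseline from repeated readings is often left to the statistical analysis plan, which is not shown, and taking the last pre-randomisation reading is conventional. This has force: the separate plan may use the score, and the choice is not an error. But the article does more than stay silent, because it defines baseline as Week 0, lists the time levels and names the optional covariates.

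The gain also rests on an assumed correlation, and a simple average can lose precision. That stands, and it shapes the fix. So does the small practical effect: at 18 per arm and ρ = 0.6, a 10% variance cut moves the adjusted 95% half-width from 1.96√(2 × 0.64/18) = 0.52 to 0.50 SD.

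A reader might infer more than the documents support:
- That leaving out the screening score biases the arm comparison. It does not; the Week 0 contrast is valid under randomisation.
- That a 25% gain is there for the taking. That needs equal correlation and the unadjusted change contrast.
- That the SDs handed to the definitive trial are inflated. Using a second pre-randomisation reading does not alter the variance of any post-treatment score.
- That the point covers other tests. CVLT-II uses a short form at screening and the standard form at Week 0, and M@T has no Week 0 reading.

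**Conclusion.** The point holds as a minor efficiency improvement for two exploratory outcomes. On the text of Sections 4.4 and 4.12, a reading already collected before randomisation is unused. Its value runs from essentially nothing, or a 1% loss after the degree of freedom, to a variance cut of 20% (adjusted) or 25% (change contrast as written). The upper figures assume equal correlation between visits. Decay over the four weeks between screening and Week 0, and selection on the screening value, both pull the gain down; neither biases the arm comparison. No progression criterion in Table 1 is affected, and the trial has no power target that the change would help to meet.

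**What to change.** Add one sentence to Section 4.12, for HBA-FAQ and PHQ-9 only: the Week 0 and screening scores both enter as covariates for the post-randomisation visits, so that the arms share the same pre-randomisation mean and the data set the weight of the screening score. A simple mean of the two readings is acceptable only if similar correlations with the outcome are expected.

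Two safeguards belong with it:
- Keep Week 0 as the reference for within-arm change, since selection at screening may shift the screening mean.
- Standardise Cohen's d on the single-visit SD. An averaged baseline has SD √((1+ρ)/2), which is 0.87 to 0.95 at ρ = 0.5 to 0.8; dividing by it would inflate d by about 5 to 15%.

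The cost is one degree of freedom per model and no new data. Section 8 says recruitment is under way, so the rule can still be set before unblinding.

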**Treatment Period: Intervention (Weeks 1–10)**							
**Feasibility**	Exit Interview *						X
**Neuropsychological Test Battery**	CVLT-II Standard Form		X			X	X
	WAIS-IV Similarities		X			X	X
	WAIS-IV Digit Span		X			X	X
	WAIS-IV Coding		X			X	X
	D-KEFS TMT		X			X	X
	Corsi Block-Tapping Test		X			X	X
	RBANS Story Recall		X		X	X	X
	EPT		X			X	X
**Neurophysiological Measures**	TMS Measurements		X	X	X	X	X
	EEG Measurements		X	X	X	X	X
**Lifestyle**	PSQI		X		X	X	X
**Functioning**	EQ-5D-5L		X		X	X	X
**Psychological Health**	PHQ-9	X	X		X	X	X
	GAD-7		X		X	X	X

**Abbreviations:** Corsi Block-Tapping Test = visuospatial working memory task; CVLT-II = California Verbal Learning Test—Second Edition; D-KEFS TMT = Delis–Kaplan Executive Function System Trail Making Test; EEG = Electroencephalography; EPT = Everyday Problems Test; EQ-5D-5L = EuroQol 5 Dimensions 5-Level; GAD-7 = Generalised Anxiety Disorder—7 Items; GHQ = General Health Questionnaire; HBA-FAQ = Healthy Brain Ageing Functional Assessment Questionnaire; M@T = Memory Alteration Test; MINI = Mini International Neuropsychiatric Interview; PHQ-9 = Patient Health Questionnaire—9 Items; PSQI = Pittsburgh Sleep Quality Index; RBANS = Repeatable Battery for the Assessment of Neuropsychological Status (Story Recall); TMS = Transcranial Magnetic Stimulation; ToPF = Test of Premorbid Function; WAIS-IV = Wechsler Adult Intelligence Scale-Fourth Edition (Similarities, Digit Span, Coding). **Note. *** Exit interview to be conducted at follow-up or whenever the participant exits the trial if withdrawing prior to completion. X indicates the assessment or procedure is performed at that timepoint.

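### As written, the mixed model gives every pair of visits the same correlation, so if correlation fades over the 18 weeks, the standard error for change from baseline at Week 18 is too small

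*Protocol article*

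**What the plan says.** Section 4.12 of the protocol article sets out the model for the secondary cognitive, functional and psychological outcomes. The fixed effects are group, "time (baseline, post-iTBS, mid-intervention, post-intervention, follow-up), and their interaction". The within-participant part is one sentence: "Participant ID will be modelled as a random effect". The section states no random slope, serial correlation or residual covariance.

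On checking, it says "Model assumptions (e.g., normality of residuals, homogeneity of variance) will be tested and corrected as needed". The results are to be effect sizes "with 95% confidence intervals to inform sample size calculations for a future adequately powered trial".

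Table 4, where "X indicates the assessment or procedure is performed at that timepoint", shows which visits enter the model:

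- **Weeks 0, 10 and 18:** CVLT-II ("CVLT-II Standard Form"), WAIS-IV Similarities, Digit Span and Coding, D-KEFS TMT, and HBA-FAQ.
- **Weeks 0, 5, 10 and 18:** RBANS Story Recall, PSQI, EQ-5D-5L, PHQ-9 and GAD-7.

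None of these is scheduled at the post-iTBS visit in Week 1.

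**The concern.** A participant random effect with independent residuals implies one variance for every visit and one correlation for every pair of visits. Two scores 5 weeks apart and two scores 18 weeks apart are treated as equally alike. The model then estimates a single residual variance and uses it for every change contrast.

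Here the gaps run from 5 to 18 weeks and span the end of training at Week 10. If scores further apart are less alike, the pooled residual variance is too small for the longest gap and too large for the shortest. Because baseline is a level of time, the group-by-time terms are differences in change from baseline, and these contrasts are the ones affected.

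Week 18 has the longest gap from baseline, and section 4.6 uses that visit to judge whether effects last. An interval that is too narrow there would make the durability estimate look more precise than it is when the definitive trial is planned.

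**Working it through.** **No planned figure to reproduce.** Section 4.7 sets 44 participants (22 per group) from precedent, without a power calculation, SD or correlation. The correlations below are therefore assumptions, shown over a range.

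**Formula.** Take complete data, unit variance at each visit and 22 per arm. Let ρ(0,j) be the true correlation between baseline and visit j, and ρ̄ the mean correlation over all visit pairs.

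- Expected residual variance under the random-intercept model: 1 − ρ̄.
- Model SE of the group difference in change: √[2(1 − ρ̄)(1/22 + 1/22)].
- True SE: √[2(1 − ρ(0,j))(1/22 + 1/22)].
- Ratio of model SE to true SE: √[(1 − ρ̄)/(1 − ρ(0,j))]. Below 1, the interval is too narrow.

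**Worked example, three visits.** Let correlation decay exponentially, with 0.70 at 10 weeks.

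- Correlations: 0.752 at 8 weeks, 0.700 at 10, 0.526 at 18. Mean 0.659, so 1 − ρ̄ = 0.341.
- Week 18: √(0.341/0.474) = 0.848. In SD units the model SE is 0.249 and the true SE 0.294.
- Week 10: √(0.341/0.300) = 1.066.

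**Same decay, four visits.** The gaps of 5, 5, 8, 10, 13 and 18 weeks give correlations 0.837, 0.837, 0.752, 0.700, 0.629 and 0.526. Mean 0.713, so 1 − ρ̄ = 0.287.

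- Week 18: √(0.287/0.474) = 0.778.
- Week 10: √(0.287/0.300) = 0.98.
- Week 5: √(0.287/0.163) = 1.33.

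**Range of SE ratios.** 'Steeper' means exponential decay, with or without a lasting participant component, and a 10-week correlation of 0.5 to 0.9. 'Mild' means 0.80 minus 0.003 to 0.006 per week of gap. At 0.003, for example, the three-visit correlations are 0.776, 0.770 and 0.746, with mean 0.764, and the Week 18 ratio is √(0.236/0.254) = 0.964.

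| Assumed pattern | Visits | Week 5 | Week 10 | Week 18 |
|---|---|---|---|---|
| Constant | 3 or 4 | 1.00 | 1.00 | 1.00 |
| Mild | 3 | – | 1.01–1.02 | 0.94–0.96 |
| Mild | 4 | 1.03–1.06 | 1.00 | 0.92–0.95 |
| Steeper | 3 | – | 1.03–1.09 | 0.83–0.90 |
| Steeper | 4 | 1.21–1.38 | 0.96–0.99 | 0.75–0.85 |

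**Coverage.** This comes from 20,000 simulated complete-data trials per setting.

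- Mild fading: Week 18 coverage 93–94%.
- Steeper fading at Week 18: 89–92% with three visits, 86–90% with four.
- Steeper fading at Week 5: 98–99%.
- Visit-specific change variance (what an unstructured covariance gives in complete data): 94.6–95.3% at every visit.

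**With dropout.** REML random-intercept fits were run with about 20% lost by Week 18 (500 trials per setting, 10-week correlation 0.70 or 0.85). Week 18 ratios were 0.75–0.84 with coverage 86–89%. Week 10 ratios were 0.98–1.04 and Week 5 ratios 1.24–1.30.

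**The case against.** The strongest reply is that the article never says the random effect is the only covariance term. A participant effect can sit alongside a structured residual, and a fuller analysis plan that is not shown may add one. That possibility stands. Still, the article gives a concrete model, and an analyst who runs it as stated gets equal correlation. The assumption-check sentence could catch unequal variances, since it names homogeneity of variance. It offers its examples without excluding others, but correlation is not among them, and fading correlation can occur with normal, equal-variance residuals. It cannot be relied on to repair this.

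The second reply is that the size depends on correlations nobody has supplied. That also stands. Under mild fading the loss is small, and the larger figures need steeper decay.

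A reader might go further than the documents allow in four ways:

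- *All Week 18 results are affected.* No. With complete data and equal variances, a plain group difference at one visit does not depend on the correlation, and section 4.12 does not name change from baseline as its target.
- *All earlier intervals are too wide.* No. Week 10 is slightly too narrow or unchanged in four-visit outcomes and only 1–9% too wide in three-visit ones. The clear excess is at Week 5.
- *The effect estimates and SDs for planning are wrong.* Not shown. With complete data, this group-by-time model gives the same mean differences under either covariance. Section 4.4 promises SDs, which can be the observed ones.
- *The decision to proceed is at risk.* No. It rests on the feasibility criteria in Table 1.

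**Conclusion.** The concern holds in a limited form. The stated model builds in equal variance and equal correlation over gaps of 5 to 18 weeks. If correlation fades, it understates the standard error of the group difference in change from baseline at Week 18: by about 4–8% under mild fading, 10–17% under steeper fading with three visits, and 15–25% with four. The direction follows from the model; the size rests on assumed correlations. If correlation is constant, the model is correct.

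The p-values are declared nominal and the outcomes exploratory, so no confirmatory claim is at stake. What suffers is the precision attached to Week 18 change effects when they inform the definitive trial. That makes this a modest point, but worth correcting because the remedy is cheap.

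**What to change.** Replace the random-effect sentence in section 4.12 with wording such as:

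> Within-participant covariance will be unstructured over the visits at which each outcome is scheduled (REML, Kenward–Roger degrees of freedom). If the model does not converge, a structure that depends on the actual time between visits (for example, a participant random intercept plus continuous-time exponential residual correlation) and then compound symmetry will be used.

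The fallback should use actual time. A heterogeneous Toeplitz structure assigns one correlation per visit step, so at Weeks 0/5/10/18 it would equate 5-week with 8-week gaps and 10-week with 13-week gaps.

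The cost is analysis wording only, with no change to visits or data collection, and the trial is still recruiting. An unstructured covariance has 3 × 4/2 = 6 parameters for three visits and 4 × 5/2 = 10 for four, which is practical with 44 participants. There is a small loss of degrees of freedom, slightly larger if dropout reaches the anticipated 20% or so (44 × 0.80 ≈ 35 at Week 18). The near-nominal coverage quoted for this option is for complete data.

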### 4.3. Interventions

#### 4.3.1. iTBS Stimulation Protocol

Participants allocated to the active stimulation group will receive iTBS over the left DLPFC across 5 consecutive weekdays. Each day comprises 5 iTBS sessions, spaced 10 min apart, totalling 25 sessions and 3000 pulses/day. Stimulation will be delivered using a MagPro x100 (MagVenture A/S, Farum, Denmark) at NICM Health Research Institute, or a MagStim Super Rapid2 Plus1 (MagStim Co Ltd., Whitland, UK) at the School of Health Sciences, each with a 70 mm figure-of-eight coil. Coil placement is guided by the Brainsight Neuronavigation System (Rogue Research Inc., Montreal, QC, Canada), using the BeamF3 algorithm to localise F3 coordinates according to the international 10–20 EEG system. The coil is held tangentially at 45° to induce a posterior–anterior current.

Resting motor threshold (RMT) will be determined using single-pulse TMS over the primary motor cortex. Surface EMG will be recorded from the right first dorsal interosseous (FDI) muscle using Ag/AgCl electrodes (active electrode on the muscle belly, reference electrode on the right olecranon), amplified ×32,000, bandpass-filtered (20–1000 Hz), and digitised at 2000 Hz via a Micro1401 Data Acquisition System and Signal software (Cambridge Electronic Design, Cambridge, UK). The motor hotspot will be defined as the scalp site where at least 5 out of 10 pulses elicit a motor-evoked potential (MEP) ≥ 50 µV in the relaxed FDI [31]. RMT will be reassessed daily, with stimulation intensity set at 75% of RMT.

Each iTBS session follows the standard protocol: bursts of 3 pulses at 50 Hz repeated at 5 Hz (every 200 ms), delivered in 2 s trains with 8 s inter-train intervals, for a total of 600 pulses per session lasting approximately 3 min. This protocol adheres to international safety and reporting guidelines for TMS [29] and the TMS Methodological Checklist by Chipchase et al. [32]. Participants may continue stable medications that do not affect cortical excitability, but substances known to lower seizure threshold (antipsychotics and recreational drugs) will be prohibited during the trial.

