### 4.9. Randomisation and Blinding

Randomisation will be implemented using REDCap with a 1:1 allocation ratio. Stratified block randomisation (block of 4 and 6) will be used, stratified by sex due to known sex differences in cognitive ageing and TMS responsiveness. The allocation sequence is computer-generated by an independent staff member and uploaded to REDCap, concealed until post-baseline assessments. Participants, outcome assessors, and data analysts will be blinded. Only the laboratory technician responsible for stimulation setup will access the allocation, solely to deliver the assigned active or sham stimulation, and will not be involved in outcome assessment or data analysis. Participants will be asked not to share their experience with others, to maintain blinding.

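### The mixed model for the secondary outcomes leaves the baseline arm difference free, so its arm contrasts are modestly less precise than the design allows; the stratum, sex, also belongs in the main model

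*Protocol article*

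**What the plan says.** The model for the cognitive, functional and psychological outcomes is given in Section 4.12: "Fixed effects will include group (CT + iTBS, CT + sham-iTBS), time (baseline, post-iTBS, mid-intervention, post-intervention, follow-up), and their interaction". Participant is the random effect. On further terms the section says: "Covariates (age, sex, education) may be included in sensitivity analyses". Neither a baseline covariate nor an equal-baseline constraint is mentioned, and site does not appear.

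Three other places bear on this:

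- Section 4.6 places the baseline assessments before randomisation.
- Section 4.9 sets out the allocation: "Stratified block randomisation (block of 4 and 6) will be used, stratified by sex". The reason given is that cognitive ageing and response to TMS differ by sex.
- Section 4.12 intends the effect sizes and their 95% intervals for the sample size of a later trial, and treats p-values as nominal.

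**The concern.** When baseline is a level of time and group has its own main effect, the model estimates a separate baseline mean for each arm. The group-by-time term for Week 10 is then the difference between arms in change from baseline. That contrast subtracts any chance baseline imbalance in full, instead of in proportion to how strongly baseline predicts the outcome. Because both arms are drawn from one population before allocation, the true baseline difference is zero. A model that does not use this fact gives away precision.

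At stake is the width of the effect-size intervals, which is the property that matters if they are to guide a later trial. A smaller matter is consistency: sex was important enough to restrict the randomisation, but the analysis leaves it to an optional sensitivity run.

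**Working it through.** **Figure to reproduce.** There is none. Section 4.7 says that "the sample size was not determined by formal power calculations for hypothesis testing", and the 44 participants rest on precedent. What can be checked is the precision of the two analyses at that size.

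**Inputs from the protocol.** 44 participants, 22 per arm, 1:1. Dropout of about 20% ("An anticipated dropout rate of ~20% has been accounted for"), which leaves 44 × 0.8 = 35.2 completers, or 17.6 per arm. Baseline is taken before randomisation.

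**Inputs assumed.** The baseline-to-follow-up correlation ρ is not given and is taken as 0.5 to 0.8. The outcome SD is set to 1 and equal at all visits. For the sex check, sex is given an effect of 0.5 SD.

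**Formulas** (n per arm, SD units):

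- Free baseline (difference in change): variance = 2 × 2(1 − ρ)/n = 4(1 − ρ)/n
- Common baseline or baseline as covariate: variance = 2(1 − ρ²)/n
- Ratio of the second to the first: (1 + ρ)/2

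For example, at ρ = 0.5 and n = 22: 4 × 0.5/22 = 0.0909, SE 0.302; and 2 × 0.75/22 = 0.0682, SE 0.261.

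| ρ | SE, free baseline | SE, common baseline | Variance cut | SE cut | 95% half-width | 44 act like |
|---|---|---|---|---|---|---|
| 0.5 | 0.302 | 0.261 | 25% | 13.4% | 0.59 → 0.51 | 59 |
| 0.6 | 0.270 | 0.241 | 20% | 10.6% | 0.53 → 0.47 | 55 |
| 0.7 | 0.234 | 0.215 | 15% | 7.8% | 0.46 → 0.42 | 52 |
| 0.8 | 0.191 | 0.181 | 10% | 5.1% | 0.37 → 0.35 | 49 |

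The last column is 44 divided by (1 + ρ)/2. With 17.6 per arm the half-widths are 0.66 → 0.57 at ρ = 0.5 and 0.42 → 0.40 at ρ = 0.8.

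Exact generalised-least-squares covariance matrices for a random-intercept model with visits at Weeks 0, 10 and 18 give the same SEs. In one generated dropout pattern at 20%, the SE goes from 0.322 to 0.285 at ρ = 0.5 and from 0.206 to 0.197 at ρ = 0.8. These calculations treat the variances and ρ as known; estimating them from 44 participants takes back a small part of the gain.

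**Sex and site, same calculation.** A main effect that is constant within a participant cancels from a change contrast.

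- Adding sex and site to the free-baseline model leaves the SE at 0.302 (ρ = 0.5, complete data).
- With 20% dropout, adding sex moves the SE by at most 0.0003.
- Adding sex to the common-baseline model takes the SE from 0.261 to 0.258 at ρ = 0.5 and from 0.1809 to 0.1802 at ρ = 0.8, a gain of about 1% or less.
- Adding site-by-time to the free-baseline model raises the SE slightly, from 0.302 to 0.304.

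**The case against.** The stated model is common and is unbiased under randomisation, so the issue is efficiency only. Baseline is not ignored, since it is modelled as a visit, and sex is named as a possible covariate. Section 4.12 does not say which contrast will be reported, so reading it as a change-score difference is an inference. The size of the loss depends on a correlation that the protocol does not give, and the outcomes are exploratory. A fuller analysis plan may exist in which covariates and contrasts are fixed. All of this stands. It limits the weight of the point but does not remove it: the fixed effects are stated in the article, the change-score reading is the natural one for a group-by-time term, and with equal variances the loss runs in the same direction for every ρ below 1.

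A reader might go further and infer that leaving out sex and site also makes the intervals too wide, or that a chance imbalance between sites stays in the arm contrast because the stimulators differ ("Stimulation will be delivered using a MagPro x100" at one site, another make at the other). The documents do not support this. A constant difference between sites cancels from change, as the calculation shows. With an assumed 50:50 split the arms' site shares would differ by chance with SD √(2 × 0.5 × 0.5/22) = 0.15, but that alone does not disturb the change contrast. What could remain is a site difference in change over time, or an active effect that depends on the device. The second would be effect modification, and a site main effect captures neither. Omitting a site term is also something that a condensed article may leave to a fuller document.

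**Conclusion.** The point holds as a modest loss of efficiency. As written, the group-by-time contrast has a variance 2/(1 + ρ) times that of a common-baseline or baseline-adjusted contrast. For ρ of 0.5 to 0.8 the better analysis cuts the Week 10 variance by 25% to 10% and the SE by about 13% to 5%. This rests on the assumed ρ, equal variances across visits, and the change-score reading of the interaction.

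Sex belongs in the main model because it is the randomisation stratum, not because of its precision gain of about 1% or less. Nothing here shows bias or an imprecision due to site.

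Nor should a reader infer that the decision to proceed is at risk. The primary analysis is descriptive, and no criterion in Table 1 uses this model. The effect is confined to the exploratory effect-size intervals.

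**What to change.** In Section 4.12, for the secondary outcomes:

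1. Constrain the baseline mean to be equal across arms in the longitudinal model, or use baseline as a covariate with the post-baseline visits at which each outcome is taken as the responses.
2. State that the arm difference at each post-baseline visit is the quantity reported.
3. Put sex in the main model as the stratification factor, and keep age and education for the sensitivity analysis.
4. If wanted, report site/device as a sensitivity analysis only.

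The cost is a few lines of analysis wording. Baseline values and sex are already collected; visits, sample size and randomisation do not change.
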